## Abstract

**Background:**

The use of early warning scores (EWSs), which integrate real-time vital sign monitoring, can help rapid response teams (RRTs) proactively identify patients at risk of deterioration. However, existing EWSs demonstrate limited evidence for the reduction of clinically important adverse events. The Visensia Safety Index (VSI) is an EWS that combines heart rate, blood pressure, temperature, oxygen saturation, and respiration rate vital sign information to generate a VSI acuity score ranging from 0, signifying the lowest risk of deterioration, to 5, signifying highest risk of deterioration. Continuous monitoring of the risk of deterioration, with alerts triggered by a score of 3.0 or greater, prompts medical attention.

**Objective:**

This protocol outlines the methodology for assessing the feasibility of combining a portable continuous vital sign monitoring system (Masimo Root Monitor) with VSI monitoring to evaluate patients at high risk of acute deterioration at The Ottawa Hospital (TOH).

**Methods:**

This 2-phase, prospective cohort study will be conducted at TOH. Patient participants will include adults (≥18 years) with high-risk conditions, such as those undergoing high-risk elective surgery, malignant hematology or oncology patients, and those admitted with infections. Exclusion criteria include patients receiving comfort care or those in specialized units requiring higher-level monitoring. Eligible patients will be monitored using the VSI with alerts to trigger rapid response team evaluation. In tandem, health care workers including physicians, nurses, and research staff who are involved in patient care and monitoring will be recruited for semistructured interviews. These interviews will explore health care providers’ clinical impressions of the VSI as an EWS to identify barriers and enablers to implementation using the Consolidated Framework for Implementation Research. Interviews will assess impressions of the monitoring technology, clinical workflow challenges, and perceptions of implementation. Data analysis will involve directed content analysis of interview transcripts to identify barriers and drivers for successful implementation. Furthermore, the feasibility of the VSI will be assessed by evaluating the proportion of continuous data successfully collected and transmitted, the timeliness of VSI-triggered alerts and their communication to the RRT team, the regular updating of the predictive tool, the rate of reported VSI-triggered events, and the completion rates of study-related tasks by research and clinical staff.

**Results:**

As of April 2025, we can report that enrollment is complete, and analysis of the results is ongoing. Interviews are still being transcribed and analyzed. We anticipate submission for publication of the results of the study by the summer of 2025.

**Conclusions:**

The execution of this prospective, mixed methods feasibility study requires a multidisciplinary effort. The study uses continuous vital sign monitoring, combined with prediction of deterioration risk, used to activate the RRT. Evaluating the feasibility and clinical impressions of this trial implementation is the first step in exploring monitoring-based predictive decision support.

**Trial Registration:**

ClinicalTrials.gov NCT05108376; https://clinicaltrials.gov/study/NCT05108376

**International Registered Report Identifier (IRRID):**

DERR1-10.2196/65360

## Introduction

Many hospitals have adopted rapid response teams (RRTs) that often include registered nurses (RNs), respiratory therapists, and physicians who provide urgent critical care expertise to assist with managing unstable patients outside of the intensive care unit (ICU) [1,2]. Early warning scores (EWSs) incorporate routinely collected data such as vital signs or laboratory results to provide a systematic, evidence-based approach for identifying vulnerable patients for assessment before a critical deterioration event [3]. Although numerous EWSs exist, many are based on a single vital sign, thereby relying on a single vital sign crossing a static threshold without accounting for trends over time or the interplay between multiple physiologic changes. For example, tools like the National Early Warning Score or Between-the-Flags primarily use fixed criteria to detect abnormalities, which can result in low sensitivity and missed detection of complex deterioration events [4]. This is in line with the traditional and current metric for monitoring deterioration with vital signs often monitored intermittently, with abnormal values flagged manually or through basic thresholds in electronic medical records [5,6]. However, this approach can delay the identification of clinical deterioration, as it may not account for trends over time or the combined significance of multiple vital sign abnormalities [6,7]. Importantly, delayed detection of patient deterioration has been associated with adverse outcomes, including higher rates of ICU admission, prolonged hospital stays, cardiac arrest, and mortality [8,9]. Recent evaluations of single vital sign–based EWS tools like the Queensland Adult-Deterioration-Detection-System and the electronic Cardiac Arrest Risk Triage Score (eCART) highlight variability in predictive accuracy, with eCART demonstrating superior sensitivity but also higher alerting rates, which can overwhelm clinical workflows [10]. Additionally, while EWS and RRT systems are widely implemented, evidence of their effectiveness in reducing hospital mortality, unplanned ICU admissions, and other adverse outcomes remains limited and of low certainty, underscoring the need for standardized outcome measures and improved methodologies in future studies [11].

In contrast to relying solely on a single vital sign for cues of deterioration, OBS Medical’s Visensia Safety Index (VSI) is an EWS that uses physiological monitoring software and machine learning to identify the likelihood of deterioration that may lead to cardiac or respiratory arrest [3,5]. As depicted in Figure 1, the VSI is a continuous measure that combines 5 vital signs—heart rate, blood pressure, temperature, oxygen saturation, and respiratory rate—into a single acuity score ranging from 0 (lowest risk) to 5 (highest risk). This score is recalculated in near real-time, with updates occurring at one-minute intervals as new vital sign data are collected. A score of 3.0, or a predetermined threshold determined based on clinical context, or greater represents a critical threshold, suggesting a significant risk of clinical deterioration and prompting an alert to the RRT [4]. The dynamic nature of the VSI allows for continuous monitoring of patient stability and early identification of deterioration trends, enabling timely interventions. Unlike traditional Early Warning Scores, VSI dynamically integrates multiple parameters into a single metric, enabling earlier and more precise detection of deterioration trends. While all five vital signs contribute to the VSI calculation, the system can operate with a minimum of three input parameters, ensuring functionality even when some data are unavailable. This capability makes VSI particularly robust for continuous patient monitoring in dynamic clinical environments.

**Figure 1 figure1:**
[figure not shown]
An infographic showing the patient setup for this study. Image created on BioRender. SpO2: oxygen saturation; VSI: Visensia Safety Index.

A retrospective cohort study of 168 patients found that 95% of the episodes of severe physiological abnormalities were identified by the VSI system and deemed valid, defined as requiring a change in clinical management [12]. A 3-phase prospective study was implemented for validation at the University of Pittsburgh Medical Centre, which included a continuous collection of cardiorespiratory variables in a non-ICU patient population [13]. Patients monitored with VSI had a statistically significant shorter average duration of any instability, shorter average duration of physiological instability, and fewer episodes of serious and persistent instability [13]. While continuous monitoring likely contributes to these outcomes, the VSI integrates multiple physiological parameters into a single predictive score, enabling earlier identification of deterioration trends compared to traditional EWS. By providing a more comprehensive and dynamic view of patient stability, VSI facilitates timely clinical interventions that may not occur with traditional monitoring systems alone [4].

A recent retrospective cohort study at The Ottawa Hospital (TOH) compared outcomes for patients who would have had an EWS alert, triggered by VSI or the National Early Warning Systems 2 (NEWS2), prior to RRT activation to patients without an EWS alert [14]. It was found that an EWS would have identified earlier deterioration for over half of the patients; however, clinical impact requires interventional study. While both the VSI and NEWS2 may have contributed to the favorable findings of early deterioration detection, EWS like NEWS2 have limitations in sensitivities, underscoring the need for more dynamic tools like VSI to improve early detection in real-world settings [5,15].

Studies involving multiparameter EWS, like the VSI, have shown promise in identifying patient deterioration earlier than clinical judgment alone, much of the existing work has been limited to proof-of-concept or validation studies, which do not address the complexities of real-world implementation. The integration of such tools into hospital workflows remains challenging due to the numerous moving parts required for successful adoption, including technical barriers, clinician buy-in, and alignment with existing clinical processes. These barriers underscore the critical need for feasibility studies that evaluate not only whether the system can be implemented within a hospital context, but also how its integration could be improved by incorporating feedback from healthcare providers. This study offers a protocol designed to address these gaps by taking a focused approach to feasibility: assessing the practicality of implementation at a single institution and identifying key barriers and enablers to facilitate smoother adoption at other sites.

The objectives of this study are to evaluate the initial clinical impressions and feasibility of using a portable monitoring system with a VSI trigger. More specifically, feasibility will be assessed by examining the proportion of continuous data successfully collected and transmitted, the frequency and timeliness of VSI-triggered alerts, the regular updating of the predictive tool, and the completion rates of study-related tasks. Clinical impressions will be explored through qualitative interviews with physicians, nurses, and research staff, focusing on barriers and enablers to implementation, perceived strengths and limitations of the system, and its integration into clinical workflows (Table 1). Overall, this protocol paper seeks to outline the methodology for evaluating the feasibility of integrating a portable continuous monitoring system using the VSI and exploring clinical impressions of its implementation to identify barriers, enablers, and potential clinical impact.

**Table 1 table1:** Description of the study’s primary objectives of feasibility and impact as well as how each will be evaluated and monitored.

Evaluation component	Objective	Objective description	Evaluation of objective
Evaluation	Feasibility	Evaluate the practicality of continuous data collection, continuous data feeding, regular updating of the predictive tool, and communication with the RRT^a^.	This study will be considered “technically feasible” if 80% of (a) continuous data are collected, (b) continuous data are fed to the predictive tool, (c) the time the predictive tool is updated on a regular basis, and (d) of triggers are reported to the RRT team.
Evaluation	Barriers and enablers to implementation	Perform a qualitative analysis of physicians, nurses, and research personnel regarding impressions of the predictive tool, perceived strengths and limitations, and perceived enablers and barriers to effective usage.	Physician, nurse, and research personnel opinions regarding impressions of the predictive tool, perceived strengths and limitations, and perceived enablers and barriers to effective usage will be evaluated through theory-driven postencounter interviews.
Impressions	Clinical impact	Compare the predictive performance of the VSI trigger to clinical gestalt.	Clinical impact will be assessed by the patient acuity rating [15], and performance measures including sensitivity, specificity, positive predictive value, and negative predictive value.

^a^RRT: rapid response team.

## Methods

### Overview

This study uses a mixed methods design to comprehensively evaluate the feasibility of implementing a portable continuous monitoring system with VSI-triggered alerts. The quantitative component focuses on assessing feasibility outcomes, such as data collection and transmission rates, VSI alert timeliness, and completion rates of study tasks. The qualitative component involves semistructured interviews with healthcare providers to explore their clinical impressions, including barriers, enablers, and perceptions of usability and integration into workflows. Together, these complementary approaches aim to provide a holistic understanding of the implementation process.

### Study Setting

This study will be conducted at both the Civic Campus and the General Campus of TOH. Each campus has a tertiary-level, mixed medical-surgical ICU with a 32-bed capacity that uses the same RRT activation criteria and institutional database, although each caters to a different patient population. Specifically, patients at the General are typically from the hematology, medical oncology, and thoracic surgery wards, whereas those from the Civic are trauma, neurology, neurosurgery, or vascular cases.

The criteria for RRT activation were defined as concerns relating to the airway, consciousness, cardiovascular system, or other markers of deterioration as deemed by clinical discretion. Data for the RRT database will be prospectively gathered by the responding RN using a standardized data collection form at the time of patient assessment.

#### Eligibility Criteria

Selection criteria for patient participants and VSI users who will participate in the subsequent semistructured interviews are outlined in Table 2. The study population will include patients outside of units with high-level monitoring, such as ICUs, as these areas already have continuous vital sign monitoring systems in place. Eligible participants will be adult patients (≥18 years) admitted to general medical or surgical wards across the two hospital campuses, which each have mixed medical-surgical ICUs with 32 beds. Patients categorized as “Category 1–Full Care” will be included as they will have no limitations on critical care interventions. Patients with “Category II, III, and IV” statuses are excluded due to goals of care that prioritize comfort or limited interventions, which do not align with the proactive monitoring and management strategies being evaluated in this study (Table 2).

**Table 2 table2:** Inclusion and exclusion criteria for patients and clinicians.

Criteria	Inclusion	Exclusion
Patient participants	Adult patients (≥18 years of age) designated for the most aggressive levels of potential intervention (Category 1 status–Full Care) belonging to any of the following: Patients who have undergone high-risk elective surgery. Malignant hematology or oncology patients at high risk for deterioration. Patients with infections admitted from the Emergency Department to the ward. Other high-risk patients determined at the discretion of RRT^a^ physicians with agreement from the patient’s MRP^b^.	Patients admitted to a unit with higher-level monitoring, including the Neurological Acute Assessment Unit, Acute Monitoring Area, Trauma Step-Down, or Intensive Care Unit. Patients in Category II, which includes full care except for CPR^c^, Category III which includes full care except respiratory or hemodynamic life support, or CPR or category IV status, which is focused solely on Comfort Care.
Visensia Safety Index users	Physicians, RNs^d^, and research personnel who consent to participate in an interview and are the enrolled patients: RRT physician or ward physician. RRT RN or ward RN. Research personnel.	Physicians, RNs, or research personnel unable to complete the interview in English.

^a^RRT: rapid response team.

^b^MRP: most responsible physician.

^c^CPR: cardiopulmonary resuscitation.

^d^RN: registered nurse.

#### Design

This study uses a prospective, mixed methods feasibility design. The enrollment and monitoring involve the patient’s most responsible physician, and members of the RRT including physicians, RNs, or respiratory therapists. Eligible patients will be identified based on the inclusion criteria listed in Table 2 and approached for potential consent. During the initial interaction, research staff will discuss the study protocol, review eligibility criteria, and assess willingness to participate. Written consent will be obtained from patients prior to initiating monitoring, A study summary is depicted in Figure 2 highlighting the study timeline and steps followed in this study.

**Figure 2 figure2:**
[figure not shown]
Visual overview of study timeline and design with emphasis on overlap in study timeline with semistructured interviews beginning 3 months after patient enrollment. RRT: Rapid Response Team.

#### Monitoring

After enrollment, the patient will be connected to a vital sign monitor (VSM). The Masimo Root monitor, a portable continuous monitoring device that integrates multiple physiological parameters, including oxygen saturation, pulse rate, and respiration rate, will be used in this study. For this study, the device is equipped with a continuous monitoring license, which allows it to perform uninterrupted data collection and enable the calculation of VSI scores. This ensures seamless monitoring and timely alert generation for high-risk patients. Research staff or the RRT RN will ensure that the patient’s data output is visible at the RRT monitoring station set up in the ICU. The monitoring system will send vital signs data to the VSI vital sign platform (VSP) server, which will process the data and calculate the VSI score, which will appear at a monitoring station set up in the ICU. VSI notifications will also be available on a mobile device carried by RRT members.

Of the 5 vital signs monitored, a minimum of 3 are required by the VSI to calculate a patient’s acuity score. To ensure accuracy, all components measuring vital signs must be appropriately connected to the patient and the VSM. As depicted in Figure 1, for the Masimo Root monitor, the patient has (1) a temperature sensor patched above the cubital fossa, (2) a finger pulse oximeter measuring oxygen saturation and pulse rate on the index finger, (3) a blood pressure cuff on either arm that intermittently inflates, and (4) a respiratory sensor placed to enable auscultation of breathing laterally to the thyroid cartilage. The RRT physician and RN can view and monitor all enrolled patients and their VSI index via the VSP front-end dashboard, which can be accessed via a standard web browser or approved mobile devices. For the Masimo VSM, viewing acuity scores across devices is only possible if the VSM is connected to a local Wi-Fi network. A visual setup of the study can be seen in Figure 1.

#### Patient and Study Team Timeline

Once the patient is on continuous monitoring, the following will be completed on a daily basis:

The patient is clinically assessed in person by the RRT, as per the standard of care for patients on the RRT roster. These assessments will include a clinical evaluation of the patient’s condition, a review of vital sign trends, and any alerts generated by the VSI.The RRT RN completes the Daily RRT visit log to capture the opinion of deterioration risk for the ward and RRT staff and the status of VSI monitoring. This includes the nurse’s assessment of the patient’s risk of deterioration based on clinical judgment, observations of vital sign trends, and any relevant changes in the patient’s condition.The RRT RN completes the RRT event log for any calls to the RRT for patients.The research coordinator completes the patient’s case report form, capturing demographic data as well as any deterioration events and outcomes.

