### Predictive Performance

The predictive performance of the VSI-triggered alerts will be compared to clinical gestalt using sensitivity, specificity, positive predictive value, and negative predictive value. Quantitative data will be analyzed using statistical software, and subgroup analyses will account for variability across patient populations and clinical settings [21].

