### Anticipated Strengths and Limitations

This study’s strengths include its use of a mixed methods design, allowing for a comprehensive evaluation of both quantitative feasibility metrics and qualitative clinical impressions. Including a diverse, multidisciplinary team, who meet regularly to discuss study progress, share insights, and document decisions and challenges throughout the study process will improve the credibility, transferability, dependability, and confirmability of results. The use of the CFIR ensures a structured approach to understanding the barriers and enablers of implementation.

A notable limitation is that this study evaluates the feasibility of integrating the VSI within a continuous monitoring system to enhance RRT workflows; however, it does not isolate the independent effects of continuous monitoring, which may itself contribute to improved outcomes or operational efficiencies. Future studies will be required to differentiate the impact of continuous monitoring alone from the added value provided by predictive tools like VSI.

While conducting this study, we anticipate learning from individual patient deployments, particularly in addressing technical requirements and troubleshooting potential issues in integrating the VSI trigger with vital sign monitoring. For instance, as depicted in Figure 1, an acoustic respiratory sensor will be used in this study which requires adequate placement and limited environmental interference (patient talking and vibrations) to be registered and used in the calculation of a VSI acuity score. Moreover, the VSM must be connected to the hospital’s Wi-Fi to sync a patient’s real-time recorded vitals and their respective VSI to the VSP front-end dashboard that can be viewed by ward or RRT staff via a web browser. Training of research personnel, RRT, and ward staff on the use and maintenance of the VSM with a VSI trigger will allow for an eased integration and use of the system. Another anticipated limitation includes, despite its proof-of-concept work in the early phases of evaluating VSI feasibility and identifying barriers and enablers to implementation, practitioners involved in the care of patients in the study must appreciate that the VSI score must be contextualized by understanding the magnitude and trend of the index as well as the clinical context. We will evaluate clinicians’ experience of the monitoring and alerts in this study.

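### The planned VSI-versus-gestalt comparison uses a risk opinion that nothing keeps independent of the VSI, so it measures VSI against VSI-informed judgement

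*Protocol article*

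**What the plan says.** The clinical-impact row of Table 1 sets the objective: "Compare the predictive performance of the VSI trigger to clinical gestalt". It names the instrument and the measures: "Clinical impact will be assessed by the patient acuity rating [15], and performance measures including sensitivity, specificity, positive predictive value, and negative predictive value". The Predictive Performance section repeats the plan: "The predictive performance of the VSI-triggered alerts will be compared to clinical gestalt using sensitivity, specificity, positive predictive value, and negative predictive value".

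The Patient and Study Team Timeline section describes how opinions of risk are collected. The RRT's daily in-person assessment includes "a review of vital sign trends, and any alerts generated by the VSI". The next item reads "The RRT RN completes the Daily RRT visit log to capture the opinion of deterioration risk for the ward and RRT staff", and the same log records the status of VSI monitoring. The section then describes the nurse's assessment of "risk of deterioration based on clinical judgment, observations of vital sign trends, and any relevant changes in the" patient's condition.

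Other sections describe who sees the VSI. Under Monitoring, RRT physicians and nurses can view every enrolled patient's index on the dashboard, and RRT members carry a mobile device with VSI notifications. Under Response Team Activation, the RRT nurse calls or visits the ward after an alert. Under Anticipated Strengths and Limitations, the display is a "VSP front-end dashboard that can be viewed by ward or RRT staff via a web browser".

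**The concern.** Comparing a score with clinical gestalt on sensitivity, specificity and predictive values is informative about the two as separate predictors only if the clinician's rating is formed without the score. Here both groups whose opinions are logged, RRT and ward, have routes to the VSI, and an RRT nurse with VSI access records both opinions. The article does not say that the rating comes before VSI viewing, or that it comes from someone without access.

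A rater who moves a patient up after an alert takes on some of the VSI's true positives and some of its false positives. A rater reassured by a quiet VSI takes on its negatives. Either way the recorded rating is no longer unaided gestalt, and the difference between the two no longer estimates what Table 1 names. Enrolment is complete and analysis is under way, and the Conclusion says the findings will inform later interventional trials. A result reported as VSI versus gestalt could therefore be carried forward under the wrong label.

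**Working it through.** **Plan's own figure.** There is none to reproduce. The article gives no sensitivity, specificity, event rate or power for this comparison, and the 70-patient target is a convenience sample. Every accuracy below is an assumption, used only to show the direction and range of the bias.

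**Step 1: is the rater exposed?**

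| Rater | Route to the VSI | Section |
|---|---|---|
| RRT nurse | Alert review is part of the daily assessment | Patient and Study Team Timeline |
| RRT nurse and physician | Dashboard and mobile notifications | Monitoring |
| Ward staff | Dashboard | Anticipated Strengths and Limitations |
| Ward staff | Call or visit after an alert | Response Team Activation |

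No section sets a rule that would break any of these links before the rating is made.

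**Step 2: model.** Let g and v be the unaided sensitivities of gestalt and VSI. Let a be the probability that a low rating is raised when there is an alert, and b the probability that a high rating is lowered when there is none. With independent errors given outcome,

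recorded gestalt sensitivity = g[v + (1−v)(1−b)] + (1−g)·v·a.

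The recorded false-positive rate has the same form, with false-positive rates in place of g and v.

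**Step 3: numbers.** Assume gestalt 50% sensitivity and 90% specificity, and VSI 70% and 85%. For a = 0.5, b = 0: sensitivity = 0.50 + 0.50×0.70×0.5 = 0.675; false-positive rate = 0.10 + 0.90×0.15×0.5 = 0.1675.

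| a | b | Recorded gestalt sens / spec (%) | VSI minus gestalt, sens / spec (points) |
|---|---|---|---|
| 0 | 0 | 50 / 90 | +20 / −5 |
| 0.5 | 0 | 67.5 / 83.25 | +2.5 / +1.75 |
| 0.75 | 0 | 76.3 / 79.9 | −6.3 / +5.1 |
| 1 | 0 | 85 / 76.5 | −15 / +8.5 |
| 0.5 | 0.5 | 60 / 87.5 | +10 / −2.5 |
| 1 | 1 | 70 / 85 | 0 / 0 |
| 0 | 0.5 | 42.5 / 94.25 | +27.5 / −9.25 |

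**Step 4: when does the sign change?** With b = 0, the sensitivity difference reverses when a > (v−g)/[(1−g)v]. Here that is 0.20/(0.50×0.70) = 0.57. For the combinations of g = 0.4–0.6 and v = 0.6–0.8 in which the VSI has the higher sensitivity, the threshold runs from 0.33 to 0.83. If the errors are correlated at 0.2 or 0.4, the 0.57 rises to 0.66 or 0.77.

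**Step 5: a second set of inputs.** Assume gestalt 60% / 80% and VSI 70% / 75%. At a = 0.5, b = 0, recorded sensitivity is 0.60 + 0.40×0.70×0.5 = 0.74 and specificity is 0.80 − 0.80×0.25×0.5 = 0.70. The sensitivity difference goes from +10 to −4 points. The threshold is 0.10/(0.40×0.70) = 0.36; at a = 0.25 recorded sensitivity is 67%, still below the VSI's 70%, so there is no reversal.

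**The case against.** The strongest reply is that the article shows exposure, not influence. Its description of the nurse's logged assessment names clinical judgment, vital sign trends and changes in condition, and does not name alerts. A reader might infer that the rating is partly a copy of the VSI, or that the nurse has always just reviewed the alerts when completing the log. Neither is supported: the first is not stated, and the second rests only on the order of items in a list. The article also does not say that the log opinion is the patient acuity rating named in Table 1; that link is inferred because no other clinician risk opinion is described. These points limit how much contamination can be asserted. They do not restore independence, because nothing keeps alerts out of the judgement being recorded.

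A reader might also infer that the comparison will come out with the wrong sign. That needs mainly upward revision, above a threshold that depends on accuracies the documents do not give. Correlated errors raise the threshold, and they are plausible because vital sign trends feed both the rating and the VSI. Timing also weakens the effect: the score updates each minute and the log is daily, so an alert after that day's rating cannot affect that rating. If half the alerts came later, an upgrade probability of 0.5 would act like 0.25, which gives no reversal in either set of inputs.

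Two further limits stand. Table 1 states a head-to-head comparison, so it should not be read as promising an estimate of what the VSI adds to clinical judgement. And the statement that the VSI does not directly lead to clinical decisions concerns management; it does not shield a risk rating from the alert.

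Leaving the matter to an analysis plan is not a full answer: analysis cannot remove exposure that was present when the rating was made.

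**Conclusion.** The concern holds as a problem of what the comparison estimates. As described, it is VSI versus VSI-informed judgement, and it cannot be reported as VSI versus unaided gestalt. That conclusion rests on the stated routes of exposure, and on the inference that the visit log supplies the gestalt measure.

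The bias is of unknown size and direction. With a true difference of +20 points in sensitivity under the assumed inputs, the scenarios shown run from −15 (always upgrading on alerts) through 0 (full deference both ways) to +27.5 (downgrading only, half the time). Reversal is possible but conditional.

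The effect is confined to the clinical-impact objective in Table 1. The 80% technical feasibility criteria and the interviews do not depend on it.

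**What to change.** **Data already collected.** Report the comparison as VSI versus VSI-informed judgement. Make no claim about VSI versus unaided gestalt except from ratings shown to precede any VSI exposure, and state this as a limitation; the current limitations text does not mention it.

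Restricting to ratings made before a patient's first alert and comparing ROC areas would not repair this. The score was already visible on the dashboard before any alert, and before the first alert the VSI is by construction below its threshold, so only the VSI's range is truncated.

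**Design and any follow-on trial.** Have ward and RRT acuity ratings entered separately and time-stamped before each rater views that day's VSI score or alerts, and report ratings made after exposure as VSI-informed.

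**Cost.** For this study, a relabelling, a check of whether any rating can be shown to precede exposure, and a limitation paragraph. The article does not show that rating times were recorded, so little or no data may support an unaided-gestalt comparison. For a later trial, a change to the order and time-stamping of the daily log, with fewer usable ratings where an alert has already been seen.
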